### Sample Size

Participants will complete the study procedure during a single chemotherapy session, specifically, the next scheduled session following inclusion. The primary outcome is the mean intensity of nausea for the first 5 days, that is, the day of the intravenous chemotherapy session and the 4 following days of the studied chemotherapy session period. We performed an a priori sample size calculation, ensuring the study to be sufficiently powered. Based on previous research,^
15
^ we aimed to detect a clinically important difference of 10 millimeters (mm) using a 100 mm Visual Analog Scale (VAS) nausea measure between the positive and neutral communication group. Assuming a 2-sided alpha of .05 and statistical power of 80%, we estimated that 198 participants (99 per communication style group) would be required. The data analysis will be conducted according to intention to treat. To allow for a potential dropout rate of 20% between inclusion and the study procedure, the study will recruit up to 240 patients.

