### Data Analysis Plan

The intention-to-treat principle will be applied when analyzing the study data, that is, all patients will be analyzed as randomized, regardless of whether they complete the study procedure as planned. The primary parameters of interests are the 2 factorial effects (2 main effect, ie, 1. communication style, and 2. treatment type, and one interaction, ie, treatment expectations) during the first 5 days of the studied chemotherapy session period. The evaluator will use a generalized linear mixed effects model (GLMM) to determine if the independent variables communication style and treatment type affect the dependent variable nausea. We take the stratified randomization into account (adjusting for random effects of department on the outcomes) and include baseline characteristics in the analysis model to increase the precision of the estimates.^
77
^ In secondary GLMMs, we will study the effects of the variety of independent variables on vomiting, QoL, and daily and physical activity. Patients who cease to participate (dropouts) and missing data will be handled according to routines as follows. In the main analysis, missing data will be handled using multiple imputations by chained equation.^
78
^ We will specify the multiple imputation model (the choice of auxiliary variables) after comparing patient characteristics between those with complete and those with incomplete data. Under the assumption that data are missing at random, an analysis based on multiple imputation conforms with the intention to treat. We will then also estimate the factorial effects using complete data only. We will conduct a sensitivity analysis by comparing estimates regarding the 2 main effects described above with estimates based on complete data only, in other words, a pattern-mixture model and tipping point analyses. Statistical significance will be defined as a 2-tailed *P* < .05, and the analyses will be performed in IBM SPSS statistics (IBM Corp, Armonk NY, USA).

In line with previous recommendations regarding cost-effectiveness analysis alongside clinical trials, we will specify the methods for cost effectiveness analysis after evaluating these outcomes. If the present evaluation shows significant health benefits on the primary outcome measure, or in at least on 1 secondary outcome, a cost-effectiveness analysis of our intervention will be conducted using a model-based approach.^
79
^

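### The missing-data sensitivity analysis is defined as a comparison with complete cases but named a pattern-mixture and tipping-point analysis; run as worded, it cannot test departures from missing at random

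*Protocol article*

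**What the plan says.** All of the relevant text is in the Data Analysis Plan of the protocol article.

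- Population: "all patients will be analyzed as randomized, regardless of whether they complete the study procedure as planned".
- Main method: "In the main analysis, missing data will be handled using multiple imputations by chained equation".
- Its assumption: "Under the assumption that data are missing at random, an analysis based on multiple imputation conforms with the intention to treat".
- A second estimation: "We will then also estimate the factorial effects using complete data only".
- The sensitivity analysis: "We will conduct a sensitivity analysis by comparing estimates regarding the 2 main effects described above with estimates based on complete data only". The same sentence goes on to restate this comparison as another thing: "estimates based on complete data only, in other words, a pattern-mixture model and tipping point analyses".

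The plan describes no departure from missing at random. It gives no shift, no assumption specific to a missingness pattern, no range and no criterion for a tipping point. No other section of the article describes a sensitivity analysis for missing data.

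**The concern.** The sentence defines a procedure and then gives it the name of a different one. A pattern-mixture analysis states how unobserved values differ from observed ones, given the data. A tipping-point analysis varies that difference until the conclusion changes. A complete-case analysis does neither. It rests on an ignorability assumption of its own and never lets the unseen nausea scores be worse than the seen ones.

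The primary outcome is patient-reported nausea intensity from a daily diary, averaged over the first five days. It is plausible that patients who feel worst fill in the diary least, although the article does not say so. If that happens to a different degree in the two communication arms, the imputed and complete-case estimates can both be biased in the same direction. A reader shown their agreement under a tipping-point label could be reassured about a threat that was not examined.

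**Working it through.** **1. What each analysis assumes.**

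| Analysis | Assumption about unobserved nausea | Is it varied? |
|---|---|---|
| Multiple imputation (main) | Same as observed, given the variables in the imputation model | No |
| Complete cases | Same as observed, given the variables in the analysis model | No |
| Pattern-mixture or tipping point | Differs from observed by a stated amount | Yes |

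The first two differ only in which variables they condition on. Comparing them shows whether the extra variables in the imputation model matter. It does not show what happens if the missing scores are worse than those variables predict.

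**2. Background figures (Sample Size section).** The target is 10 mm on a 100 mm scale, two-sided alpha .05, power 80%, 99 per communication group. The SD is not stated. With n = 2(1.96 + 0.84)² SD²/10² per group, SD 24 gives 91, SD 25 gives 99 and SD 26 gives 107. The stated size is therefore consistent with an SD of 25. That value is back-solved, so it is an assumption below.

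**3. Size of a possible bias.** Let m be the fraction of one arm's scores that is missing, and d the amount by which their true mean is worse than imputed. The effect shifts by m × d.

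| m | d = 20 mm | d = 30 mm |
|---|---|---|
| 5% | 1 mm | 1.5 mm |
| 10% | 2 mm | 3 mm |
| 20% | 4 mm | 6 mm |

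Both m and d are assumptions. If m × d is the same in both arms, the shifts cancel.

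**4. What a real tipping-point analysis would report.** Assume SD 25, 99 per arm, an observed difference of 10 mm and the same fraction m missing in each arm. Only the positive-communication arm's imputed values are shifted. SE = 25 √(2/[99(1 − m)]), and the tipping shift is (10 − 1.96 SE)/m.

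- m = 5%: SE 3.65, shift about 57 mm
- m = 10%: SE 3.75, shift about 27 mm
- m = 20%: SE 3.97, shift about 11 mm

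A result of that size would be hard to overturn with 5% missing and much easier with 20%. The planned comparison cannot tell these cases apart.

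**5. Simulation.** Settings (all assumed): true difference 0, SD 25, 99 per arm, about 20% missing per arm, one covariate with correlation 0.3, 10 imputations, 1,500 runs. Estimates are positive minus neutral communication, so a negative value favours positive communication.

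| Scenario | Complete cases: estimate (rejection rate) | Imputation: estimate (rejection rate) | Mean absolute gap |
|---|---|---|---|
| Missing completely at random | +0.2 mm (5.7%) | +0.2 mm (5.7%) | 0.43 mm |
| High nausea drives missingness, positive arm only | −4.5 mm (23.2%) | −4.5 mm (22.7%) | 0.41 mm |
| Same, +25 mm added to imputed positive-arm scores | −4.5 mm (22.9%) | +0.5 mm (4.3%) | 4.98 mm |

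The gap between the two planned analyses is the same with and without bias. The third row follows from step 3: 0.20 × 25 = 5 mm, and −4.5 + 5 = +0.5 mm.

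Two limits apply. The imputation model here holds the same covariate as the analysis model, so the two estimates agree closely by construction. Strong auxiliary variables could separate them, but would still leave untested whatever those variables do not explain. The +25 mm shift was chosen knowing the mechanism, which in practice is unknown; that is why a range is needed.

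**The case against.** The strongest reply is that the sentence is clumsy rather than wrong in intent. The preceding sentence already provides for the complete-data estimation, so the authors may have meant the next one to add a pattern-mixture model and tipping-point analyses as further work. Both are standard departures from missing at random, and their shift range and criterion would normally stand in an analysis plan, which is not shown. This may well be so, and the lack of detail is not the point here. But the wording equates the comparison with the two methods, and an analyst who follows it would run only the comparison.

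It can also be said that a large effect of arm-specific missingness is not established. Patients are blinded to communication allocation, which makes strongly different non-response less obvious. Non-responders are sent reminders, although by post about 1 to 2 weeks later, which is late for a question about the past 24 hours. This stands as a limit on the size, not on the misdefinition.

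Three stronger readings are tempting, and the article does not support them.

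- A reader might infer that the trial claims robustness to data not missing at random. It does not; it presents missing at random as an assumption.
- A reader might infer from "We will specify the multiple imputation model (the choice of auxiliary variables) after comparing patient characteristics" that only variables differing between completers and non-completers can enter the imputation model. The text neither says only nor excludes balanced predictors, and baseline characteristics are in the analysis model anyway. The Randomization and Blinding section keeps the evaluator blinded until after the primary analysis, so the choice would largely be made blind.
- A reader might take the 20% in the Sample Size section as the diary-missingness rate. It is dropout between inclusion and the study procedure, before the therapist receives the allocation.

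**Conclusion.** The point holds as a misdefined analysis. The only missing-data sensitivity analysis in the article is a complete-case comparison carrying the name of two methods that it is not. If it is run as worded, departures from missing at random go untested. The primary analysis itself is unaffected.

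The reasoning on method rests on no figure. The size does: 1 to 6 mm across 5% to 20% missing in one arm, with unseen scores 20 to 30 mm worse than imputed. Those inputs, the SD of 25 and the link between nausea and diary non-response are all assumptions. The upper end needs the whole departure to fall in one arm. The change should be made because it is cheap and the check is otherwise uninformative on this question, not because a bias of that size has been shown.

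**What to change.** Split the sentence in two.

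1. Keep the comparison with complete-data estimates as a separate supplementary analysis, under that name.
2. Define the tipping-point (pattern-mixture) analysis as delta-adjusted multiple imputation. After imputation, add a shift to the imputed nausea scores, varied separately by communication arm, and refit the primary model. A grid of 0 to 30 mm in 5 mm steps is a reasonable start. Extend it if the conclusion has not changed, since step 4 shows that the tipping shift can exceed 30 mm when little is missing. Report the shift, or pair of shifts, at which the primary P value crosses .05, together with the fraction of scores missing in each arm so that readers can judge its plausibility.

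The cost is one rewritten sentence and modest extra programming. No design change or additional data collection is needed.

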**Methods::**

This is a trial protocol for a randomized, sham-controlled, patient- and evaluator-blinded clinical trial. Patients (n = 198 patients according to a sample size calculation) with breast, colorectal, or bladder cancer undergoing neo-/adjuvant moderately to highly emetogenic chemotherapy are being randomized in 2 × 3 factorial design to the following conditions: 1. neutral or 2. positive communication style regarding expected treatment effects, during the antiemetic treatment types: A) standard care only (including antiemetics, no acupuncture), or, in addition to standard care, B) sham acupuncture with telescopic non-penetrating needles, or C) verum, penetrating acupuncture. The 2 communication styles 1 and 2 are carried out during the antiemetic treatments given by an intervention therapist immediately pre and post (20 minutes × 2) an intravenous chemotherapy session. Data are being collected at baseline on the day before the chemotherapy session, daily for 10 days, at a 10-day follow-up, and at a follow-up after completing the entire chemotherapy period, lasting about 6 months. Primary outcome is mean score Visual Analog Scale nausea grading for the first 5 days of the chemotherapy session period. Secondary outcomes are for example, vomiting, treatment expectations, QoL, daily and physical activity, and physiological measures. Treatment effect modifiers will be analyzed, for example, blinding success, treatment expectations, and previous nausea experiences.

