Self-reported descriptive data: On a baseline questionnaire, patients supply sociodemographic data (eg, sex, age, level of education, profession), clinical data (eg, comorbidities, disease-specific variables, medications), data on previous experience of and belief in acupuncture effects,^
22
^ data on previous nausea experiences in their lives and specifically when undergoing cancer therapy, self-predicted risk for nausea,^
36
^ and data regarding therapeutic alliance, for example, to which extent the patient trusts the therapist to be able to help him/her.^
61
^

Data on nausea and vomiting: Patients complete a measure of nausea and vomiting^
7
^ daily for 10 days, answering questions about the primary outcome (nausea intensity) and the secondary outcomes (nausea occurrence, duration of nausea, vomiting episodes, and consumption of antiemetics). This measure asks the following questions with reference to the past 24 hours: “Have you experienced nausea?” (“No” / “Yes”); “How intense was the nausea?” A 100 mm VAS with verbal anchors “No nausea” and “Worst possible nausea” is used. The accumulated duration (in minutes) of nausea within the past 24 hours is registered. Patients also respond to the questions: “Have you vomited?” (“No”/“Yes”), “How many episodes?” (number of episodes is given), and “Have you consumed rescue antiemetics?” (“No”/“Yes”). They are asked to: “Please detail agent, dose and frequency of each antiemetic agent used.” Also, other kinds of nausea and vomiting-related care consumption is self-registered. Burden is asked for and registered on 2 separate 100-mm VAS: “Did the nausea negatively affect your daily life?.” The same question is posed regarding vomiting, both anchored with 0 (“Not affected at all”) and “100” (“Affected in the worst possible way”; Figure 2).

Expectations data: Patients rate their treatment expectations daily for 10 days, using a valid expectancy measure,^
56
^ “Do you believe that the treatment you are going to receive is effective for nausea and vomiting?” This is measured using a 100 mm VAS anchored with 0 (“I don’t believe at all that it’s effective”) and 100 (“I completely believe that it’s effective”). Post-treatment, the question is written with the modified verb tenses “received” and “was.”

Treatment satisfaction data: On day 10 after the intervention, patients rate their interest in receiving future acupuncture treatment by answering the questions^
37

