^ “If you should need similar chemotherapy in the future, would you be interested in receiving antiemetic acupuncture treatment?” (“Yes, completely interested,” “Yes, very interested,” “Yes, moderately interested,” “Yes, a little interested,” “No, not interested”), and “If you should experience other problems in the future that could be treated with acupuncture, would you be interested in receiving acupuncture treatment?” (“Yes, completely interested,” “Yes, very interested,” “Yes, moderately interested,” “Yes, a little interested,” “No, not interested”). After completion of the entire chemotherapy period, patients rate the self-perceived overall nausea intensity, and the burden of it, for the entire chemotherapy period,^
7
^ as well as the overall perceived effect of the antiemetic treatment,^
37
^ using 3 different 100 mm VAS anchored with 0 and 100 (labeled “No nausea” and “Worst possible nausea”; “No burden” and “Worst possible burden”; and “Not effective at all” and “Completely effective,” respectively).

QoL data: Patients repeatedly (Figure 2) respond to the Swedish version^
62
^ of Functional Assessment of Cancer Therapy—General (FACT-G).^
63
^ The 27-item FACT-G covers 4 domains on health-related QoL: physical wellbeing (7 items), social wellbeing (7 items), emotional wellbeing (6 items), and functional wellbeing (7 items), graded on a numerical rating scale from 0, “completely disagree” to 4, “completely agree.” Higher scores on the domains and the total score indicate better QoL. Patients also grade their health-related QoL on the Swedish version^
64
^ of the Euroqol-5 Dimensions-3 Levels (mobility, self-care, usual activities, pain/discomfort, anxiety/depression), and Euroqol-VAS, a 100 mm vertical scale anchored with 100, “best imaginable health state” and 0, “worst imaginable health state.”^
65
^ Further, responses are given to a single-item question regarding global QoL.^
66
^

Daily and physical activity data: Daily activities (often mentioned as “everyday activity,” or “activities of daily living”) the preceding week are assessed using 7-graded statements ranging from “I managed all my daily activities” to “I did not manage any of my daily activities.”^
67
^ Physical activity performance is assessed using widely used self-report questions^
68

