## Discussion

The present study aims to determine whether therapists’ positive communication about antiemetic effects may strengthening treatment expectations when undergoing antiemetic treatment using standard care, sham acupuncture or verum acupuncture and thus affects nausea and vomiting, QoL, and capacity in daily and physical activity. Additionally, the study investigates the cost-effectiveness of this kind of communication and treatment procedure.

Systematic reviews have stressed the potential for benefits from antiemetic treatment procedures, which include acupuncture^24,25^ and caring procedures involving communication intended to reinforce patients’ hope and positive treatment expectations.^42,49^ Several researchers have pointed out the lack of knowledge regarding whether findings from non-clinical experimental studies on the effects of information and communication can also be seen in clinical settings with patients.^39,44
[Bibr bibr45-15347354251361464]-46^ Psychosocial interventions have the potential to induce clinically relevant effects on chemotherapy-induced nausea and vomiting,^
80
^ for example, information on how to manage symptoms during chemotherapy significantly improved patients’ QoL.^
81
^ A review showed that a positive outlook and uplifting spirit on the part of healthcare personnel gave patients hope and inspiration.^
83
^ However, we do not yet know whether the characteristics of the communication, positive or neutral, play any significant role in the antiemetic effects experienced by patients undergoing emetogenic chemotherapy.

The primary outcome of the present study is nausea, as it is one of the most burdensome side effects among patients undergoing chemotherapy.^5,15^ Based on patient-experiences supporting the beneficial effects of positive treatment expectations and communication during chemotherapy,^
9

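### The cost-effectiveness methods are to be chosen after the outcomes are known, and the analysis run only after a significant benefit; this permits selection on the results, of a size the protocol does not fix

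*Protocol article*

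**What the plan says.** All the operative text is in the last part of the Data Analysis Plan (Methods).

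- **Timing of the methods:** "we will specify the methods for cost effectiveness analysis after evaluating these outcomes". The sentence refers to earlier recommendations on economic evaluation alongside trials.
- **Condition for running it:** "If the present evaluation shows significant health benefits on the primary outcome measure, or in at least on 1 secondary outcome". The general threshold is given just before: "Statistical significance will be defined as a 2-tailed *P* < .05".
- **The one element named in advance:** "a cost-effectiveness analysis of our intervention will be conducted using a model-based approach".

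The outcomes that can open the gate are an open list. The Abstract says "Secondary outcomes are for example, vomiting, treatment expectations, QoL, daily and physical activity, and physiological measures", and Data Collection adds, for the daily measure, "the secondary outcomes (nausea occurrence, duration of nausea, vomiting episodes, and consumption of antiemetics".

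The opening paragraph of the Discussion puts the aim without any condition: "Additionally, the study investigates the cost-effectiveness of this kind of communication and treatment procedure".

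**The concern.** Two separate things are decided by the trial results.

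1. **The methods.** A 2 × 3 design offers several comparisons: positive v neutral communication, verum v sham, and acupuncture v standard care. It also offers many effect measures, from nausea intensity to the EQ-5D-3L and sick leave. If these are settled once it is known which comparison and which outcome did well, the choice can follow the result. Under Randomization and Blinding, the evaluator is blinded only until the primary outcome has been analysed, so blinding does not protect this later step.
2. **Whether the analysis exists.** An effect estimate that is used only when it, or something correlated with it, has crossed a significance threshold is too large on average. Cost-effectiveness depends on incremental cost and effect with their joint uncertainty. A gate on significance of effect alone would discard a non-significant benefit that came with lower costs, and the Discussion itself hopes for less rescue medication and lower societal costs.

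At stake is the credibility of a cost-effectiveness claim, and the match between what the Discussion promises and what the Methods would deliver.

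**Working it through.** **The plan's own figure.** Sample Size gives a 10 mm difference, two-sided alpha 0.05, 80% power and 99 per communication style (198 in total). No SD is stated. Solving for it: SD = 10 / (1.960 + 0.842) × √(99/2) = 25.1 mm. With SD = 25 mm the formula returns 99 per group and a power of 0.804, so 198 is reproduced. SD 25 mm remains an assumption; SD 20 would need 126 in total and SD 30 would need 284.

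Standard error of the communication contrast: SE = 25 × √(2/99) = 3.55 mm.

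**Step 1. A gate on one outcome that feeds its own estimate.** With μ = true effect / SE, the mean estimate given z > 1.96 is SE × [μ + φ(1.96 − μ) / (1 − Φ(1.96 − μ))].

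| True effect | Mean given significance | Ratio (SD 25) | Ratio (SD 20 to 30) |
|---|---|---|---|
| 10 mm | 11.2 mm | 1.12 | 1.04 to 1.24 |
| 7.5 mm | 10.0 mm | 1.33 | 1.16 to 1.53 |
| 5 mm | 9.2 mm | 1.83 to 1.84 | 1.53 to 2.16 |

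This is not the gate in the plan, which opens on any one of several outcomes.

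**Step 2. The gate as written, no true effect.** The number of outcomes k is not fixed by the protocol; I assume 6 to 11 including the primary. A two-tailed 0.05 test gives 0.025 in the direction of benefit. If the outcomes are independent, the chance that the gate opens is 1 − 0.975^6 = 0.14 to 1 − 0.975^11 = 0.24. By simulation with correlation 0.5 it is 0.10 to 0.15.

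**Step 3. The gate as written, nausea as an input fixed in advance.** Simulation with k = 6 or 11 and correlation 0 to 0.5; overestimation of the nausea effect given that the gate opened:

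| True nausea effect | Same standardised effect on all outcomes | Effect on nausea only |
|---|---|---|
| 10 mm | 0 to 1% | 9 to 12% |
| 7.5 mm | 0 to 7% | 22 to 33% |
| 5 mm | 1 to 28% | 42 to 77% |

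With no true effect anywhere, the fixed input averages 0.2 to 1.2 SE above zero, which is about 0.6 to 4.2 mm.

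**Step 4. The input picked after the results.** If the most favourable outcome is taken, its mean given an open gate is about 2.4 SE when the truth is zero (2.4 × 3.55 = 8.5 mm on the nausea scale). It is 2.7 to 2.8 SE when every true effect is 1.12 SE (20% power per outcome), so the ratio is 2.7/1.12 = 2.4 to 2.8/1.12 = 2.5.

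**Step 5. Methods against Discussion.** Under the Methods, no cost-effectiveness analysis follows if no outcome shows a significant benefit. The Discussion sentence allows for no such case. Both cannot stand as worded.

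**The case against.** The best defence has five parts.

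- **The size.** A reader might infer that the cost-effectiveness result will be inflated by 12%, 33% or 83%. The documents do not support that. Those figures describe a gate on the primary outcome alone, feeding its own estimate. Under the gate as written, inflation can be close to nil. This stands.
- **The input.** Millimetres of nausea need not enter the model. The protocol collects a utility instrument, the Swedish version "of the Euroqol-5 Dimensions-3 Levels (mobility, self-care, usual activities, pain/discomfort, anxiety/depression), and Euroqol-VAS", and gives no planning figures for it. A model-based analysis may also use inputs from outside the trial, and the gate does not act directly on costs. So it is not established that the result is biased upward. What can be said is that inputs tied to the gate can be too favourable. This stands.
- **The choice.** A reader might infer that the most favourable outcome and comparator will be used. The text speaks only of the methods in general; late specification permits such a choice but does not show that it will be made. This stands.
- **The null case.** A reader might infer that a null primary result leaves no economic analysis. It does not: one significant secondary outcome is enough to open the gate.
- **Standing of the aim.** Cost-effectiveness is not in the twofold objective, the main hypothesis or the Abstract, and the conflict rests on one Discussion sentence. The authors also cite recommendations for their sequence, which cannot be checked here. This lowers the weight of the point.

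One defence fails: that a full protocol or an analysis plan not shown may hold the details. The article does not merely leave the methods out. It states that they will be set after the outcomes are evaluated, so an economic plan written earlier would contradict it.

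**Conclusion.** The point holds as a matter of sequence and consistency. The Methods commit to choosing the cost-effectiveness methods after the outcomes and to running the analysis only after a significant benefit, while the Discussion states the aim without condition. This leaves room for selection on the results, and effect inputs that are gating outcomes or correlate with them can favour the intervention too much. No scenario examined gave a material bias the other way.

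The size is open. With an assumed SD of 25 mm and 6 to 11 outcomes, it runs from about 0 to 1% (large effects throughout, input fixed in advance) to roughly 10 to 80% (effects small or confined to the outcome used). It is larger still if the input is picked afterwards. Severity is on the lower side: the primary estimate, sample size and error rate of the trial are untouched, and only a conditional downstream analysis is affected.

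**What to change.** Before the allocation codes are broken, write and date a short health-economic plan that sets:

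- the comparisons (for example positive v neutral, verum v sham, acupuncture v standard care);
- the outcome measure, for example the EQ-5D-3L already collected;
- perspective, time horizon and cost items;
- how uncertainty will be shown.

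Replace the significance condition in the Data Analysis Plan with a commitment to run the analysis whatever the P values, using the full-sample estimates with their uncertainty. With no gate, the bias from conditioning on it is zero. Then reconcile the Data Analysis Plan and the Discussion, so that both describe the same unconditional aim.

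Cost: a few pages written earlier than intended, and a small analysis even after a null result. No new data or patients are needed.
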